# Study Design

This is a German multi-center, observer-blind, randomized, and actively controlled parallel-group study to compare after a successful series of routine electroconvulsive therapy (ECT) the overall effectiveness of maintenance ECT (mECT) plus treatment as usual (TAU) versus TAU only in subjects aged from 18 to 65 years with the indication of clozapine resistant schizophrenia.

A schematic of the study design is shown below:

[figure not shown]

**Phase I:** Subjects will be included in the study according to the inclusion and exclusion criteria and will receive an ECT series with a maximum of 18 ECT treatments based on a clinical indication for ECT or until there is a clinically sufficient response to treatment.

**Phase II:** Subjects who respond to ECT in phase I (BPRS score < 70% of BPRS at visit 1) meet the inclusion criteria for phase II of the study. After completing the ECT series in phase I and before starting phase II, subjects are randomized to receive either maintenance ECT plus standard treatment or standard treatment alone.

## Planned Interim Analysis

No interim analysis is planned.

## Overall Duration of the Study

The study will be conducted over a period of 54 months.

The duration of the study may be extended and additional sites may be added depending on the observed rate of recruitment.

| Total study duration: | 54 months |
| --- | --- |
| Duration of the clinical phase: | 39 months |
| FSI (First Subject In): | Q1/2025 |
| LSLV (Last Subject Last Visit): | Q2/2028 |
| Statistical analyses completed: | Q4/2028 |

The study end is defined as “last subject last visit” (LSLV).

In case of an early termination of the study (see chapter 7.4), the date of the early termination will be the date for end of study.

## Duration of Study Participation for each Subject

The study consists of:

- Screening and stabilization phase: max. 1 week
- Phase I (ECT): max. 6 weeks
- Phase II (maintenance ECT + TAU or TAU): 28 weeks
- Follow-up period: 12 months

In total the duration of the study for each subject is expected to be at maximum 20 months.

## Measures to Minimize Bias

- - 1. Randomization

Subjects will be randomized 1:1 by the site staff using REDCap (eCRF), which maintains allocation concealment by accepting subjects’ inclusion before assigning the treatment. Block randomization will be applied stratified by subjects taking clozapine at visit 2 and subjects not taking clozapine at visit 2 but not site in order to prevent predictability of allocation.

- - 1. Rater/Observer-Blinding

The interviews regarding BPRS will be videotaped at baseline (visit 2) as well as at any planned and/or unplanned visit at which a subject is experiencing a worsening of its condition. The videos will be edited to remove any hints about treatment, and brief (2–5 seconds), nonessential portions from all tapes will be erased to create 3–10 skips in a random fashion, thus balancing the presence of awkward skips that might be otherwise present mostly in the ECT tapes. An independent, blinded rater (psychologists and psychiatrists trained in the assessment of psychopathological symptomatology) will score the edited tapes.

The primary endpoint is combined endpoint of judgements by blinded and unblinded non-study related raters (see section 2.1). Strictly speaking, the study is only partially observer blind. Blinding of the observer at the site is impossible because the patients usually reveal their actual treatment during assessments. Therefore, it is justifiable from a medical point of view to call the study observer-blind.

# Subject Selection

## Number of Subjects and Sites

A total of 140 subjects will be enrolled in the study (phase I) and 84 subjects will be randomized (phase II), i.e. 42 subjects per treatment group (see chapter 9.9).

The study will be national and multicenter.

It is intended that the study will take place at approximately 14 German sites.

## Inclusion Criteria

Subjects meeting all of the following criteria will be considered for enrollment in the study:

- Current schizophrenia according to Diagnostic and Statistical Manual of Mental Disorders, Fifth Edition (DSM-5)
- BPRS total score > 45
- History of clozapine resistant schizophrenia (CRS), which will include treatment-resistant schizophrenia with clozapine intolerance or absolute contraindications for clozapine
- Age between 18 and 65 years

## Exclusion Criteria

Subjects presenting with any of the following criteria will not be included in the study:

- Diagnosis of DSM-5 major neurocognitive disorder (“dementia”), current severe substance-use disorder, affective disorders with psychotic symptoms or any personality disorder
- Inability to read/write German or inability to provide written informed consent
- Pregnancy or breast-feeding
- General medical condition contraindicating ECT

# Study Intervention

## Description of Study Intervention

**Electroconvulsive Therapy (ECT)**

ECT will be performed with right unilateral electrode placement (RUL). The stimulation dose will be six times the seizure threshold based on titration during the first session. If subjects do not show a clinical response after six treatments, electrode placement will be switched to bilateral electrode placement. Propofol or ketofol (esketamine + propofol) will be used as hypnotics. Time to stimulation will be 3-4 minutes after administration of the hypnotic. Succinylcholine will be used as a muscle relaxant in the absence of contraindicatons. Flumazenil will only be used if subjects are treated with a lorazepam equivalent dose > 4 mg/day. Glycopyrronium bromide will be used to minimize hypersalivation. Esmolol and urapidil will be used to treat postictal hypertension. Electrode placement, stimulation dose, medications used during ECT, time to stimulation, postictal suppression index, midictal amplitude, maximum sustained coherence, motor seizure duration, and EEG seizure duration will be recorded in the eCRF.

**Phase I:** All subjects receive a full course of routine ECT (max. 18 sessions; 3x/week)

**Phase II:** Subjects who are randomized to the experimental intervention group will additionally receive mECT. The maintenance ECT is administered according to a fixed schedule: Intervals will be one mECT per week for the first 6 mECTs, followed by one mECT every two weeks for 5 mECTs and then one mECT every three weeks for 4 mECTs (until week 28).

**Treatment-as-usual** (**TAU)**

All subjects in phase II will receive treatment according to current guidelines, including a stable continuation of the initial antipsychotic treatment (that was given concurrently to the acute ECT course in Phase I).

**Stabilization (before start of phase I)**

The stabilization period before the start of phase I will serve to implement any major changes to the medication that might be necessary before the initiation of the ECT series.

## Concomitant Medication and Therapy

There are no restrictions regarding concomitant medication and therapy during study participation.

# Study Visits and Investigations / Assessments

This section describes the procedures and assessments required to be performed at specified study visits as outlined in the schedule of assessments. For details on the individual assessments please refer to section 6.2.

The interventions/assessments will be recorded in the source documents and the eCRF.

**Screening Visit / stabilization phase**

- Review of inclusion/exclusion criteria
- Obtaining written informed consent

**Phase I**

- Study visits 1 and 2 with psychometric assessments
- Full course of routine ECT (max. 18 sessions; 3x/week)
- Randomization (at the end of visit 2) of subjects with improvement of 30% or more on the Brief Psychiatric Rating Scale (BPRS)

**Phase II**

- First mECT should be administered within 1 week after randomization
- Study visits 2a-e and 3 with psychometric assessments are done on the day of the third, sixth, eighth, tenth twelfth or fifteenth maintenance ECT, respectively, for the intervention group. Thinc-it and MMSE must be assessed before the treatment is administered, the remaining psychometric assessments can be performed before or after mECT is administered.
- Intervention group: TAU + mECT
- Control group: Only TAU

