| Mini Mental State^6^ Examination |  | **x** | **x** | **x** | **x** | **x** | **x** | **x** | **x** | **x** | **x** | **x** |
| THINC-it ®^6^ |  | **x** | **x** | **x** | **x** | **x** | **x** | **x** | **x** | **x** | **x** | **x** |
| Northoff Catatonia Rating Scale (German version) |  | **x** | **x** |  |  |  |  |  | **x** | **x** | **x** | **x** |
| Q-LES-Q-18 |  | **x** | **x** |  |  |  |  |  | **x** | **x** | **x** | **x** |
| Self-Stigma of Mental Illness Scale – Short Form |  | **x** | **x** |  |  |  |  |  | **x** | **x** | **x** | **x** |
| Stigma-Stress-Scale |  | **x** | **x** |  |  |  |  |  | **x** | **x** | **x** | **x** |

ECT: Electroconvulsive Therapy; mECT: Maintenance Electroconvulsive Therapy; TAU: treatment as usual; THINC-it: THINC integrative tool; Q-LES-Q-18: Abbreviated Quality of Life Enjoyment and Satisfaction Questionnaire

*Stabilization: implementation of any major medication changes before the initiation of the ECT series

** The times indicated as weeks refer to the TAU group, however the respective mECT should be scheduled within the respective week. Visit 2 is regarded to take place in week 0, e.g. calendar week 20. For the patients receiving mECT, the first mECT should be scheduled in the next calendar week, e.g. calendar week 21, and the 3^rd^ mECT (Visit 2a) should take place in calendar week 3 after V2, e.g. calendar week 23. A calendar week is from Monday to Sunday. Two mECTs cannot be performed in the same calendar week

^1^ Sociodemographics: Age, sex, education, marital status, residence

^2^ Vital signs: height, weight

^3^ All baseline characteristics (including vital signs, medical history, prior medication, …) must be assessed **before** randomization. Randomization should be carried out only in subjects with improvement of 30% or more on the Brief Psychiatric Rating Scale (BPRS).

^4^ According to randomization

^5^ Treatment depending on patients’ choice

^6^ Mini-Mental State Examination (MMSE) and Thinc-it must be performed before mECT is administered.

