# Study Objectives and Endpoints

## Primary Objective and Primary Endpoint

The main purpose of the study is to show superiority of maintenance electroconvulsive therapy (mECT) plus treatment as usual (TAU) versus TAU only.

The primary endpoint is the time to relapse for which relapse is defined as Brief Psychiatric Rating Scale (BPRS) ≥20% higher than individual BPRS at start of phase II at any following study visit or any unscheduled readmission due to a worsening of psychiatric symptoms or any unscheduled visit with an BPRS ≥20% higher than individual BPRS at start of phase II.

The BPRS is evaluated by an unblinded rater at the site and a blinded central rater. Hospital readmission is decided by unblinded non-study related staff. The first relapse decision is used for analysis.

If the condition of a patient is worsening (assessed by unblinded staff), the BPRS assessment is videotaped for the evaluation by the blinded rater.

The time to relapse is the most important outcome parameter, when the effectiveness of interventions in subjects with schizophrenia is investigated. The BPRS is a widely used instrument in psychiatry for the assessment of psychotic symptoms and has been implemented in previous clinical trials and large-scale investigations (33). The instrument has been internationally validated and proven to be sensitive to change.

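### In the mECT arm only, the BPRS rating that defines relapse may be taken before or after the same-day session, in an order left to unblinded site staff.

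*Protocol*

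**What the plan says.** Protocol section 6 (Phase II) says that visits 2a to 2e and visit 3 "are done on the day of the third, sixth, eighth, tenth twelfth or fifteenth maintenance ECT, respectively, for the intervention group". In the Schedule of Assessment, "The times indicated as weeks refer to the TAU group", and section 6 describes that arm as "Control group: Only TAU", so its visits follow the calendar with no session attached.

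Footnote 6 of the Schedule states that "Mini-Mental State Examination (MMSE) and Thinc-it must be performed before mECT is administered". Section 6 repeats this rule for the two cognitive tests and then adds that "the remaining psychometric assessments can be performed before or after mECT is administered". The Schedule lists the BPRS at each of these six visits. No other section times it relative to the session or sets a minimum recovery interval.

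Under section 2.1, "relapse is defined as Brief Psychiatric Rating Scale (BPRS) ≥20% higher than individual BPRS at start of phase II at any following study visit". A second route to relapse is "any unscheduled readmission due to a worsening of psychiatric symptoms", and a third is the same BPRS rise at an unscheduled visit. The first relapse decision counts, whether it comes from the site rater or the blinded central rater. Section 5.1 describes the anaesthesia: "Propofol or ketofol (esketamine + propofol) will be used as hypnotics".

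**The concern.** The protocol shields two cognitive measures from the acute effect of a session but leaves the scale behind the primary endpoint unprotected. A BPRS taken hours after a seizure and a general anaesthetic is measured in a state that no control subject is ever in. Sedation or confusion could raise the score; a transient lift in mood could lower it.

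Two features make this more than a nuisance. First, the first crossing of the threshold is final, so a transient rise cannot be corrected at a later visit. Second, the order is open at each visit, and the people who set it know the arm; section 3.4.2 concedes that the site observer cannot be blinded. If the order is not recorded, no later analysis can separate ratings made before a session from those made after it.

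The blinded central rating is not a full safeguard. The taped interview may itself be held after the session, and a subject's manner may hint at the arm despite editing.

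**Working it through.** **1. Which ratings are exposed.** Section 5.1 gives six weekly sessions, then five at two-week intervals, then four at three-week intervals. The sessions therefore fall in weeks 1–6, then 8, 10, 12, 14 and 16, then 19, 22, 25 and 28, which agrees with the visit weeks in the Schedule. The time since the last session at a BPRS rating is then:

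| Visit | Session no. (week) | Previous session (week) | Rated before | Rated after |
|---|---|---|---|---|
| 2a | 3 (3) | 2 (2) | about 1 week | hours |
| 2b | 6 (6) | 5 (5) | about 1 week | hours |
| 2c | 8 (10) | 7 (8) | about 2 weeks | hours |
| 2d | 10 (14) | 9 (12) | about 2 weeks | hours |
| 2e | 12 (19) | 11 (16) | about 3 weeks | hours |
| 3 | 15 (28) | 14 (25) | about 3 weeks | hours |

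The two permitted orders thus measure different things, and the gap widens as phase II goes on. In the TAU arm no such choice exists.

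**2. How far a score must move.** Entry requires a BPRS above 45 (section 4.2), and randomisation requires at least 30% improvement. At exactly 30% improvement, the relapse margin is 0.20 × 0.70 × entry score:

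- entry 46: reference 32.2, margin 6.4 points
- entry 60: reference 42.0, margin 8.4 points
- entry 80: reference 56.0, margin 11.2 points

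A larger improvement in phase I makes the margin smaller.

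**3. The plan's own figures.** Section 9.9 counts missing values as relapses:

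- TAU: 0.15 + 0.85 × 0.85 = 0.8725
- mECT + TAU: 0.30 + 0.70 × 0.45 = 0.615

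The monthly hazards −ln(1 − p)/6 are 0.3433 and 0.1591, so the hazard ratio is 0.4634. Expected events are 42 × (0.8725 + 0.615) = 62.5. Schoenfeld power is 0.860 and a log-rank simulation gives 0.861, against 0.85 stated. With an mECT hazard of 0.17 the power is 0.800, against about 80% stated. These figures reproduce and do not depend on when the BPRS is taken.

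**4. What a timing effect could do (illustration only).** The documents give no effect size. Assume that post-session rating changes the apparent total mECT hazard by 10%, 20% or 30%, and simulate 42 per arm with censoring at 6 months:

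- No true effect (both hazards 0.3433) and relapses hidden: the two-sided rejection rate rises from about 5% to about 8%, 16% and 30%.
- Planned effect and false relapses added: power falls from 0.86 to about 0.77, 0.67 and 0.54.

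These are large shifts to assume. In the planned mECT arm, observed relapses make up only 0.70 × 0.45 / 0.615 = 0.315 / 0.615 = 51% of the events; the rest are missing values counted as relapses. Taking the share of events as a rough share of the hazard, a 20% change in the total would need a change of about 0.20 / 0.51 = 39% in observed relapses, and only some of those come from scheduled ratings.

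**The case against.** The best defence is that the split is deliberate. Section 1.3 names cognitive effects as the most common side effect of ECT in phase I, so the cognitive tests are fixed before the session and the clinician-rated scales are left flexible. Nothing contradicts itself here, and post-session rating is permitted, not required. The documents contain no evidence that a same-day session changes a BPRS score. All of this stands, and it limits the severity. It does not give a reason for leaving the primary scale unstandardised.

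A reader might infer several stronger things that the documents do not support:

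- **That the trial is biased towards mECT.** Masked worsening would favour mECT; post-ictal confusion or sedation would count against it. The direction cannot be determined.
- **That all six ratings of all 42 mECT subjects are affected.** This is a ceiling. Sites may rate beforehand, relapse ends the intervention (section 7.2), and 30% missing values are expected in this arm.
- **That a per-visit error rate can be stated.** Suppose a reference BPRS of 35, a mean change of 2 to 5 points and an SD of 8. The per-visit chance of crossing is then 27–40%. Over six visits, treated as independent, that is 84–95% relapse, far above the 45% (61.5% with missing values) in section 9.9. Spread evenly, those planning rates imply about 9.5% and 14.7% per visit. Correlation between visits would narrow the gap, but the inputs have no source in the protocol.
- **That the visit 2 reference adds to the asymmetry.** It is taken one day after the last ECT of phase I, before randomisation, and is the same for both arms.
- **That the tape reveals the arm.** Sections 3.4.2 and 12.2 require editing that removes treatment cues, and section 3.4.2 adds random skips. A residual hint is possible, not certain.

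Section 9.9 does mention bias from differing observation schedules, but only as a scenario in which power is lower. That does not control an error that favours mECT.

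**Conclusion.** The point holds as a one-arm lack of standardisation in the scheduled-visit BPRS component of the primary endpoint. It rests on three readings of the text: all scheduled phase II visits of the mECT arm fall on session days; the BPRS is covered by the before-or-after permission; and no other section times it. The relapse margin is about 6.4 to 8.4 points for entry scores of 46 to 60 at exactly 30% improvement, so a modest acute shift could matter for a subject near the threshold.

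The size and direction of any bias are unknown, and the error rates in the working depend wholly on assumed hazard changes. Readmissions and unscheduled-visit relapses are not tied to a session day. This should be fixed because it is avoidable and cheap to remove, not because a distortion has been shown.

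**What to change.** In section 6 (Phase II) and footnote 6 of the Schedule of Assessment, extend the before-session rule to the BPRS interview (site rating and tape) and to the other clinician-rated scales on visit days. Record the time of rating relative to the session in the eCRF. If a rating has to be done on another day, require that it precede that week's session; a day that is merely free of mECT could fall just after one and would bring the problem back.

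The cost is a small scheduling burden on mECT mornings, when these subjects must already complete MMSE and THINC-it before the session. All mECT-arm scheduled ratings would then sit at the end of the interval between sessions, which is at least a defined and uniform condition. Sample size and stated power stay as they are.

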**Visit 3**

Study participation can regularly end at study visit 3.

If the study participation ends prematurely (before visit 3), see section 7.3, the assessments according to visit 3 should be done.

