# SCHEDULE OF ASSESSMENT

| **Phase (duration)** | **0** | **I** | | **II** | | | | | | **Follow-Up** | | **Unscheduled**  **Visit** |
| --- | --- | --- | --- | --- | --- | --- | --- | --- | --- | --- | --- | --- |
|  | max. 1 week | Initial ECT series  (max. 6 weeks and max. 18 ECTs are allowed) | | 28 weeks | | | | | | 12 months | |  |
| **Visit** | **Screening/ inclusion** | **1** | **2** | **2a** | **2b** | **2c** | **2d** | **2e** | **3** | **4a** | **4b** |  |
| **Time** | Before start of stabilization*  (max. 7 days before visit 1) | 1-2 day(s) before the first ECT | 1 day after last ECT (week 0) | 3rd calendar week ** or  on the day of the 3rd mECT | 6^th^ calendar week after V2 or  on the day of the 6th mECT | 10^th^ calendar week after V2 or on the day of the 8th mECT | 14^th^ calendar week after V2 or on the day of the 10th mECT | 19^th^ calendar week after V2 or on the day of the 12th mECT | 28^th^ calendar week after V2  or on the day of the last mECT | 6 mo. after visit 3 | 12 mo. after visit 3 |  |
| Informed Consent | **x** |  |  |  |  |  |  |  |  |  |  |  |
| In-/Exclusion Criteria | **x** |  |  |  |  |  |  |  |  |  |  |  |
| Sociodemographics^1^ |  | **x** |  |  |  |  |  |  |  |  |  |  |
| Medical History |  | **x** |  |  |  |  |  |  |  |  |  |  |
| Concomitant Medication / Therapy |  | **x** | **x** | **x** | **x** | **x** | **x** | **x** | **x** | **x** | **x** | **x** |
| Vital Signs^2^ |  | **x** |  |  |  |  |  |  | **x** |  | **x** | **x** |
| Randomization^3^ |  |  | **x** |  |  |  |  |  |  |  |  |  |
| Adverse events |  |  |  | **x** | **x** | **x** | **x** | **x** | **x** | **x** | **x** | **x** |
| **Intervention** |  |  |  |  |  |  |  |  |  |  |  |  |
| TAU or mECT + TAU |  |  |  | **x**^4^ | **x**^4^ | **x**^4^ | **x**^4^ | **x**^4^ | **x**^4^ | **x**^5^ | **x**^5^ |  |
| **Questionnaires/tests** |  |  |  |  |  |  |  |  |  |  |  |  |
| Brief Psychiatric Rating Scale |  | **x** | **x** | **x** | **x** | **x** | **x** | **x** | **X** | **x** | **x** | **x** |
| Global Assessment of Functioning |  | **x** | **x** | **x** | **x** | **x** | **x** | **x** | **x** | **x** | **x** | **x** |
| Positive and Negative Symptom Scale |  | **x** | **x** | **x** | **x** | **x** | **x** | **x** | **x** | **x** | **x** | **x** |
| Hamilton Rating Scale for Depression |  | **x** | **x** | **x** | **x** | **x** | **x** | **x** | **x** | **x** | **x** | **x** |

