## Secondary Objectives and Endpoints

The secondary objectives are to compare side effect profile and safety as well as psychopathological changes between mECT plus TAU versus TAU only.

The secondary endpoint for treatment efficacy is the proportion of relapse free subjects at the end of phase II.

Further secondary endpoints are:

- BPRS
- Global assessment of functioning (GAF) allowing a general (34) and PANSS allowing a differentiated view on specific symptom dimensions (35)
- HAMD (36) monitoring depression, since ECT and mECT have a well-known positive influence on mood
- The Northoff catatonia rating scale (NCRS-dv) (37) assessing the full spectrum of catatonic symptoms
- Q-LES-Q-18, an abbreviated and validated Quality of Life Enjoyment and Satisfaction Questionnaire for subjects with schizophrenia (38)
- The Self-Stigma of Mental Illness Scale – Short Form (SSMIS-SF) (39) and the Stigma-Stress-Skala (40) are used for self-labeling and stigma
- MMSE (41) and THINC-it (28-30) monitoring cognition

All secondary endpoints listed above are analyzed at the end of phase II and at the end of follow-up.

Safety will be also determined by the frequency of adverse events from randomization up to the last follow-up visit.

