## Early Termination of the Study

Early termination is defined as the premature end of a clinical study before at least the last patient has completed visit 3 .

The following reasons or events may result in an early termination:

- New findings on the study intervention lead to doubt as to the benefit-risk ratio;
- Subject enrollment is insufficient;
- DSMB recommends termination of the entire study or single treatment arms.

An early end of the study due to early inclusion of the total number of subjects is not considered an early termination. In the event of premature discontinuation of the study for any reason whatsoever, the regulatory authorities should be informed according to applicable regulatory requirements. In case of an early termination of the study, the date of early termination will be the date of end of study.

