## General Considerations

Further analyses will be defined in the statistical analysis plan (SAP) which has to be authorized before analysis commences by the biometrician and the sponsor. All below mentioned analyses will be described in greater detail in the SAP.

The primary analysis will be conducted when all subjects completed visit 3 of the trial. An additional analysis will take place when all subjects completed the follow up.

SAS version 9.4 or higher will be used for analyses.

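### Section 6 lets a subject finish regularly at visit 3, while the rest of the protocol counts the 12-month follow-up as part of each subject's participation, so the end-of-follow-up comparison may rest on a self-selected subset

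*Protocol*

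**What the plan says.** Two sets of statements bear on whether a randomised subject is expected after visit 3.

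**Visit 3 as a regular end.** Section 6, Visit 3: "Study participation can regularly end at study visit 3". The sentence that follows it treats an end as premature only when it comes before visit 3. Section 7.4 uses the same landmark: the study is terminated early only if it stops "before at least the last patient has completed visit 3".

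**Follow-up as part of the study.**
- Section 3.3, whose heading refers to each subject, lists "Follow-up period: 12 months" among the study components and adds: "In total the duration of the study for each subject is expected to be at maximum 20 months".
- The Schedule of Assessment has columns for 4a and for 4b ("12 mo. after visit 3"), with no sign that either is optional. Its footnote 5 leaves the treatment in this period to the patient; it says nothing about leaving attendance to the patient.
- Section 2.2: "All secondary endpoints listed above are analyzed at the end of phase II and at the end of follow-up". Safety is the "frequency of adverse events from randomization up to the last follow-up visit".
- Section 9.3: "An additional analysis will take place when all subjects completed the follow up".

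**The concern.** The protocol does not settle whether 4a and 4b are expected from everyone. If sites use the permission, the subjects seen at 4b are those who chose to go on. That choice may depend on how well a subject is and on interest in further mECT, and both may follow from the randomised arm. The comparison at the end of follow-up would then no longer be between the groups as randomised.

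Three rules add to this:
- Section 9.5 categorises the scales with relapse and dropout as extra categories. A relapse-free subject who finishes regularly at visit 3 is neither.
- The models in section 9.5 are fitted per time point, so a subject not seen at 4b contributes nothing to the 4b model.
- Section 8.3 ends adverse event observation at the last study visit, so observation could differ by up to 12 months between subjects, possibly unequally by arm.

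This cannot simply be left to the analysis plan. Who is expected at a visit is fixed by the protocol, and no later analysis recovers visits that were never sought.

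**Working it through.** **1. Does the stated maximum include follow-up?** Section 3.3 gives at most 1 week of screening and stabilisation, at most 6 weeks of phase I, 28 weeks of phase II and 12 months of follow-up.

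1 + 6 + 28 = 35 weeks; 35 / 4.345 = 8.1 months; 8.1 + 12 = 20.1 months.

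This reproduces the stated 20 months. The figure is reached only with the full follow-up; a subject who finishes at visit 3 has at most about 8 months. Follow-up is thus 12 of the 20 months.

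**2. Side by side.**

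| Question | Section 6, Visit 3 | Elsewhere |
|---|---|---|
| Is leaving at visit 3 regular? | Yes | 3.3 and the Schedule provide no such exit |
| When is follow-up complete? | Not addressed | 9.3: when all subjects have completed it |
| How is a relapse-free leaver classed at 4b? | Not premature | 9.5: only relapse and dropout are added categories |

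The clearest clash is with section 9.3: its condition has no defined meaning if some subjects may properly finish at visit 3.

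**3. How many could be seen at 4b?** Section 9.9 plans 42 subjects per arm and expects phase II withdrawal of 15% (TAU) and 30% (mECT + TAU).

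- TAU: 42 × 0.85 = 35.7
- mECT + TAU: 42 × 0.70 = 29.4
- Together: 65.1, about 65 of 84 at visit 3

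The protocol gives no retention rate for the follow-up year. For illustration only:

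| Share of the 65 continuing (assumed) | TAU | mECT + TAU | Total with 4b data |
|---|---|---|---|
| 100% | 35.7 | 29.4 | 65.1 |
| 80% | 28.6 | 23.5 | 52.1 |
| 50% | 17.9 | 14.7 | 32.6 |

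These rows use the same share in both arms. They show loss of numbers, not the bias, which depends on who stays.

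The rows also assume that subjects who relapsed still attend. If relapse ended participation, the planning rates of 87.25% and 61.5% (which count missing as relapse) would leave 42 × 0.1275 = 5.4 and 42 × 0.385 = 16.2, about 22 subjects, before anyone left by choice.

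**4. What is not touched.** Section 9.4 censors subjects without relapse at visit 3, and the sample size in section 9.9 uses phase II inputs only. With hazards 0.3433 and 0.1591 and 42 × (0.8725 + 0.615) = 62.5 expected events, Schoenfeld's formula gives power 0.86 against the stated 0.85. No follow-up quantity enters.

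**The case against.** The best defence is that the protocol describes a core trial to visit 3 with a follow-up attached. The sentence in section 6 is a permission. Section 3.3 gives an expected maximum, which an earlier end does not breach. Section 2.2 names analysis times without stating that everyone must be seen then. Section 7.4 fits this reading, section 9.3 calls the later analysis additional, and treatment in follow-up is by choice anyway. All of this stands, and it limits the point to an inconsistency with a consequence for secondary results. It does not remove it: section 9.3 still waits for all subjects, and nothing else marks 4a and 4b as optional.

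Some stronger readings are tempting but not supported:
- **That section 6 ends participation at visit 3, or that 2.2 and 3.3 make follow-up compulsory.** Neither wording goes that far.
- **That there would be no record of why subjects left.** Section 7 asks for any reason given on withdrawal, section 10.1 wants missing data explained, and section 10.3 wants them clarified before lock. The gap is narrower: it is unclear whether these rules reach someone whose exit is regular.
- **That late entrants cannot reach 4b.** A 39-month clinical phase less 20 months leaves 19 months of entry, but section 3.2 allows extension and defines study end by the last subject's last visit. The sum would be the same without the section 6 sentence.
- **That 50% to 80% of all 84, or 42 to 67, would contribute.** This base ignores the protocol's own withdrawal rates; 67 exceeds the 65 expected at visit 3.

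**Conclusion.** The inconsistency is real and should be resolved, but it concerns the end-of-follow-up results only. As written, the efficacy and cognition scales at 4b and the adverse event comparison over follow-up may rest on a self-selected subset, with regular leavers unclassified. That continuation will in fact depend on outcome or arm is plausible but not shown by the document.

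The extent cannot be derived. About 65 of 84 subjects at visit 3 follows from the stated withdrawal rates, provided relapsed subjects remain in the study. The range of about 33 to 52 with 4b data rests on the further assumption that 50% to 80% continue. The primary endpoint, its power and the end-of-phase-II endpoints stand as planned.

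**What to change.** Decide which reading is meant and word it the same way throughout.

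**If follow-up is for everyone:** remove the permission under Visit 3 in section 6. State that 4a and 4b, at their existing times, are expected for every randomised subject who has not withdrawn consent, including those who relapsed or stopped mECT. Record the reason for anyone who does not continue past visit 3, and count such subjects as dropouts in the follow-up analyses. This is the better choice for the comparison by arm.

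**If follow-up is optional:** say so in the Schedule of Assessment and in sections 2.2, 3.3, 6 and 9.3. Report the end-of-follow-up results as descriptive for those who continued, with numbers and reasons by arm.

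While editing the Visit 3 text, correct its reference for premature end: it points to section 7.3 (Temporary Halt), whereas discontinuation is in 7.2.

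The cost is wording, since the visits are already scheduled. The small downside of the first option is that sites must pursue 4a and 4b for subjects they might otherwise release.
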